# 1. Research Background and Rationale

## 1.1 Chemotherapy-Induced Nausea and Vomiting (CINV)

To this day, chemotherapy remains a cornerstone of cancer treatment. However, it is crucial to pay adequate attention to the associated adverse effects. The most common of these is chemotherapy-induced nausea and vomiting (CINV), which is directly related to a decline in quality of life and impairs patients' ability to manage daily activities[1, 2]. According to international guidelines (e.g., the American Society of Clinical Oncology (ASCO), the National Comprehensive Cancer Network (NCCN), the Multinational Association of Supportive Care in Cancer (MASCC), or the European Society for Medical Oncology (ESMO)), the current standard antiemetic treatment for patients receiving moderately emetogenic chemotherapy (MEC) to highly emetogenic chemotherapy (HEC) involves a three-drug regimen, typically including a neurokinin-1 (NK1) receptor antagonist (RA), a 5-hydroxytryptamine-3 (5-HT3) RA, and corticosteroids, with or without olanzapine. Among these, dexamethasone (DEX, oral/intravenous) is administered at preventive doses of 8 mg, 12 mg, or 20 mg on the first day (depending on the accompanying antiemetic drugs), followed by oral or intravenous administration of 8 mg for 2 to 3 days after chemotherapy [3-5].

Despite the long-standing use of DEX as part of the classic antiemetic regimen, its associated side effects should not be overlooked. These side effects may lead to metabolic abnormalities, glaucoma, cataracts, impaired wound healing, dyspepsia, hypertension, increased risk of infection, and increased risk of osteoporosis or osteonecrosis [6]. When combined with immunotherapy, the dosage of DEX also needs to be controlled. Netupitant and palonosetron capsules (NEPA) is a combination formulation consisting of netupitant and palonosetron, which can effectively target two key antiemetic pathways and may help reduce the dosage of DEX in CINV management. Therefore, we intend to explore the possibility of further reducing the total dosage of DEX when combined with NEPA before MEC/HEC administration.

## 1.2 Current Treatment and Research Status of CINV

The current guidelines recommend a multimodal regimen for preventing nausea and vomiting induced by moderately to highly emetogenic chemotherapy, typically including a 5-HT3 RA, an NK-1 RA, and multi-day dexamethasone, with or without olanzapine.

In a multicenter, placebo-controlled, Phase III study, Ito Y TT et al. conducted a non-inferiority trial comparing single-day versus multi-day standard-dose dexamethasone in patients receiving HEC. The results showed that when combined with an NK1-RA and palonosetron, dexamethasone could be tapered in the subsequent days without additional drug toxicities (46.9% vs. 44.0%, 95% CI, 212.6%-6.8%; P=0.007) [7]. However, this study reported that in the delayed phase, the complete control rate was higher in the 3-day dexamethasone group than in the single-day standard-dose group, suggesting that a 3-day dexamethasone regimen might be more appropriate for patients with risk factors for CINV. Subsequently, Celio L and Cortinovis D et al. validated the non-inferiority of shortening the dexamethasone course in patients receiving high-dose cisplatin, achieving study endpoints across all time intervals in this clinical trial [8]. As early as 2014, R.J. Gralla et al. conducted another Phase III study, demonstrating that NEPA, when combined with DEX, had a slight but consistent numerical advantage (2%-7%) in the total complete response (CR) rate over aprepitant plus palonosetron in consecutive cycles [9].

There are limited studies on reducing the dosage of DEX, and thus the appropriate dosage of antiemetics when NEPA is combined with MEC or HEC remains uncertain. A recent study published in 2023 showed that when patients received a single dose of 8 or 12 mg DEX on Day 1 before each HEC cycle, combined with single-day NEPA treatment, complete response rates of >95% were observed in both the acute and delayed phases, with all patients achieving a 100% CR rate from the third cycle onward [10]. A randomized Phase III study by Celio L et al. showed that neither of the two reduced-dose DEX groups demonstrated a significant impact of vomiting on the daily life of patients receiving high-dose cisplatin, with a DEX dose of 12 mg in DEX1 [11]. Another recently published Phase III study also confirmed the efficacy and safety of 12 mg DEX plus NEPA in elderly patients receiving cisplatin, with similar CR rates across treatment groups [12].

In summary, NEPA may help reduce the dosage of DEX in preventing CINV, optimize the use of DEX, and benefit patients with contraindications and side effects related to corticosteroids, offering a more convenient and durable alternative to the classic multimodal antiemetic regimen. Therefore, the combination of dexamethasone and NEPA for the treatment of CINV appears promising. This drug regimen has the distinct advantages of convenient administration and good compliance, and more evidence-based medical evidence is needed. Previously, we explored the efficacy and safety of single-day low-dose dexamethasone combined with single-day netupitant and palonosetron capsules for preventing CINV, with a total CR rate of approximately 85%. Therefore, our research team plans to further explore the efficacy and safety of single-day different low-dose dexamethasone combined with single or double doses of netupitant and palonosetron capsules in the treatment of CINV.

### **1.3 Potential Risks and Benefits**

#### **1.3.1 Known Potential Risks**

Any drug or therapy at any stage of the study may present unforeseen and potentially severe toxicities and adverse effects. The primary risk for patients with chemotherapy-induced nausea and vomiting is the impact on food intake. For patients requiring radical concurrent chemotherapy for their tumors, CINV can lead to a decline in quality of life and physical function, resulting in reduced chemotherapy doses, delayed chemotherapy, or even termination of chemotherapy, thereby affecting the anti-tumor treatment process and efficacy, and potentially increasing mortality.

The current guidelines recommend a multimodal regimen for preventing nausea and vomiting induced by moderately to highly emetogenic chemotherapy, typically including a 5-HT3 RA, an NK-1 RA, and multi-day dexamethasone, with or without olanzapine. Although DEX has been used as part of the classic antiemetic regimen for many years, its associated side effects should not be overlooked. Vardy JL et al. conducted a survey on the side effects of dexamethasone for preventing CINV, summarizing moderate to severe adverse reactions including insomnia (45%), gastrointestinal symptoms (27%), anxiety and irritability (25%), increased appetite (18%), weight gain (17%), rash (15%), depression after discontinuation of treatment (7%), hiccups (7%), and oral candidiasis (3%). Among the 60 patients receiving MEC who participated in this survey, only 15 patients (25%, 95% CI 15-38%) reported no

side effects or only mild side effects, while 19 patients (32%, 95% CI 20-45%) reported at least three moderate to severe symptoms [13]. Given the high rate of reported symptoms, these side effects may outweigh the benefits of dexamethasone when used with moderately emetogenic chemotherapy. Another review also pointed out that corticosteroid therapy may lead to side effects such as metabolic abnormalities, central nervous system effects, glaucoma, cataracts, acne, impaired wound healing, dyspepsia, myopathy, hypertension, increased risk of infection, or hypothalamic-pituitary-adrenal axis suppression [14]. A dose-dependent sensation of perineal itching lasting several minutes after dexamethasone administration has also been reported in clinical trials [15].

A 2023 open-label, randomized controlled study by Gao A et al. in patients receiving HEC regimens showed the superiority and good safety of double-dose fosaprepitant over single-dose fosaprepitant in preventing delayed-phase CINV when using the same doses of palonosetron and dexamethasone [18]. Inspired by this, we conducted a second round of trials based on the previous treatment study, selecting patients from the control and experimental groups who did not achieve complete absence of nausea and vomiting in the first cycle for a second cycle of treatment. The primary and secondary endpoints in the second cycle were self-controlled with those in the first cycle, exploring the efficacy and safety of single-day different low-dose dexamethasone combined with double-dose standard NEPA in preventing nausea and vomiting induced by moderately to highly emetogenic chemotherapy. Although NEPA has shown good safety in multiple clinical trials and clinical observations, there are limited studies on the use of multiple doses of netupitant and palonosetron capsules in preventing nausea and vomiting induced by MEC/HEC, and no studies have been conducted on the use of NEPA after chemotherapy. The instructions also state that NEPA should not be used to prevent nausea and vomiting after chemotherapy, making this an off-label use with unknown risks and the potential for unforeseen and severe toxicities and adverse effects.

Based on the existing safety clinical data of dexamethasone and netupitant and palonosetron capsules, adverse events reported by similar products, and the characteristics of the study population, the following measures have been taken in risk control: (1) Strictly adhering to the inclusion and exclusion criteria for participants, excluding those with severe, uncontrolled comorbidities, as well as diseases or clinical conditions that may interfere with the evaluation of the drugs; (2) Closely monitoring adverse events (AEs) in participants during the study, including AEs and AEs of special concern, such as significant gastrointestinal reactions and new drug-induced rashes, and providing suggested management measures; (3) Permitting rescue treatment in the trial at the investigator's discretion, including reducing the dose of dexamethasone, substituting other antiemetic drugs, delaying chemotherapy, reducing chemotherapy doses, or temporarily discontinuing chemotherapy.

### **1.3.2 Known Potential Benefits**

The potential benefits for participants in this study are the reduction of chemotherapy-induced nausea and vomiting in a more convenient and durable manner, thereby further improving quality of life and avoiding the need to reduce chemotherapy doses or delay chemotherapy, or even suspend chemotherapy. Indirect benefits include reducing adverse reactions associated with antiemetic drugs, such as insomnia, gastrointestinal symptoms, anxiety and irritability, rash, increased risk of infection, etc. Completing chemotherapy at full doses, full courses, and on schedule will also improve treatment outcomes and prognosis for cancer patients.

## **2. Research Objectives and Endpoint Goals**

### **2.1 Research Objectives**

#### **2.1.1 Primary Objective**

To explore the efficacy of single-day different low-dose dexamethasone combined with single dose of standard NEPA in preventing nausea and vomiting induced by moderately to highly emetogenic chemotherapy.

#### **2.1.2 Secondary Objectives**

To evaluate the safety of single-day different low-dose dexamethasone combined with single dose of standard NEPA in preventing nausea and vomiting induced by moderately to highly emetogenic chemotherapy.

### **2.2 Research Indicators**

#### **2.2.1 Primary Endpoint**

Proportion of subjects with complete response (defined as no vomiting and no rescue medication within 7 days after receiving the study drug).

### **2.2.2 Secondary efficacy Endpoints:**

CRR during acute (0-24h), delayed (24-120h), and long-delayed (120-168h) phases

### **2.2.3 Secondary Safety Endpoints**

Treatment related adverse events (evaluated using the National Cancer Institute Common Terminology Criteria for Adverse Events (NCI CTCAE) version 5.0).

### **2.2.4 Exploratory endpoints**

1. TCR and CCR during acute, delayed, long-delayed, and overall post-chemotherapy phases.
2. CINV incidence patterns and daily occurrence rates across each period.

## **3. Study Design**

This study is a randomized controlled non-inferiority clinical trial conducted at Xiamen University Zhongshan Hospital, which will be registered at Chinese Clinical Trial Registry (ChiCTR) prior to participant enrollment. The study groups include the control group and the experimental group. The trial consists of screening period and treatment period.

### **3.1 Screening Period**

Inclusion and exclusion criteria are evaluated. Those who meet the criteria can enter the treatment period.

### **3.2 Treatment Period**

(1) Control Group: 8 mg of dexamethasone is administered intravenously 0.5 hours before chemotherapy, and 1 tablet of netupitant and palonosetron hydrochloride capsules (each containing 0.3 g of netupitant and 0.5 mg of palonosetron hydrochloride) is taken orally 1 hour before chemotherapy.

(2) Experimental Group: 5 mg of dexamethasone is administered intravenously 0.5 hours before chemotherapy, and 1 tablet of netupitant and palonosetron hydrochloride capsules (each containing 0.3 g of netupitant and 0.5 mg of palonosetron hydrochloride) is taken orally 1 hour before chemotherapy.

Stratification Factors: Gender, age, patient's risk factors for CINV, ECOG score, tumor type, distant metastasis of the tumor, emetogenic risk of the chemotherapy regimen, smoking history, and drinking history, etc.

Drug Discontinuation Criteria During Treatment: Subjects should discontinue the drug if they experience severe adverse events or specific types of adverse events, such as severe drug intolerance or allergic reactions.

## 4. Selection and Withdrawal of Study Subjects

### 4.1 Inclusion Criteria

Subjects must meet all the following inclusion criteria to be enrolled in this study:

1. Age 18-75 years old.
2. Diagnosed with malignant tumors and undergoing chemotherapy regimens with moderate to high emetogenic risk.
3. ECOG score 0-1.
4. Expected survival of  $\geq 12$  weeks at screening and able to receive the current anti-tumor treatment for at least one cycle.
5. Adequate organ function meeting the following criteria:
  - a: Neutrophil count  $\geq 1.5 \times 10^9/L$ ;
  - b: Platelet count  $\geq 100 \times 10^9/L$ ;
  - c: In patients without known liver metastases, aspartate aminotransferase  $\leq 3 \times$  ULN and/or alanine aminotransferase  $\leq 3 \times$  ULN (for patients with liver metastases, it can be relaxed to  $\leq 5 \times$  ULN);
6. Eligible subjects of childbearing age must agree to use reliable contraceptive measures throughout the study period (including male or female condoms, contraceptive foams, gels, films, creams, suppositories, abstinence, and intrauterine devices, etc.), except for female subjects who have undergone

hysterectomy, bilateral salpingectomy, bilateral tubal ligation, or have been postmenopausal for more than one year, and male subjects who have undergone bilateral vasectomy or ligation.

7. Voluntary participation in this study, signing the informed consent form, and good compliance.

## 4.2 Exclusion Criteria

Subjects with any of the following conditions are not eligible for this study:

1. Received radiotherapy within one week before chemotherapy.
2. Suffer from other diseases that cause nausea or vomiting except those caused by tumor chemotherapy drugs, including but not limited to gastrointestinal obstruction and central nervous system malignancies.
3. Experienced vomiting, nausea, or mild nausea within 24 hours before treatment.
4. Concurrent use of corticosteroids or any other possible antiemetic drugs.
5. Contraindications to corticosteroids.
6. Cognitive impairment (such as dementia or severe learning difficulties) that prevents completion of nausea and vomiting-related evaluation scales, etc.
7. Use of antipsychotic drugs within 30 days before the start of treatment or during treatment.
8. Severe and uncontrolled diseases affecting the liver, kidneys, cardiovascular, respiratory, endocrine systems, or the central nervous system.
9. Allergy to the study drugs.
10. Pregnant or lactating women.
11. Participated in any other clinical study of investigational drugs or devices within three months before screening.
12. The investigator deems that participation in the trial poses a significant risk to the subject's health or safety or may affect the assessment of efficacy for other reasons.

### 4.3 Withdrawal Criteria

Patients will be withdrawn from the study if any of the following occurs:

1. The subject withdraws informed consent to participate in the study or requests to withdraw from the study and refuses further follow-up.
2. The investigator deems it necessary to withdraw the subject from the study for other reasons, such as the subject losing the ability to express their will due to imprisonment or isolation, etc.
3. Loss to follow-up.
4. Serious adverse events where risks outweighed benefits.
5. The investigator or regulatory authority requests termination of the study.

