| Withdrawal Criteria | 
Patients will be withdrawn from the study if any of the following occurs:
 
 
1. Withdrawal of informed consent or request to exit the study and refusal of further follow-up.
 
2. Investigator deems it necessary to withdraw the patient (e.g., loss of freedom to express willingness due to imprisonment or quarantine).
 
3. Loss to follow-up.
 
4. Serious adverse events (SAEs) where risks outweighed benefits
 
5. Termination of the study by the sponsor, investigator, or regulatory authority.
 
                                                                                                         |
| Study Design        | 
This study is a randomized, non-inferiority trial with control and experimental groups, divided into screening and treatment phases.
 
 
1. Screening Phase           
 
• Assess eligibility criteria. Eligible patients proceed to the treatment phase.
 
 
 
2. Treatment Phase           
 
• Control Group: Intravenous injection of 8 mg dexamethasone 0.5 hours before chemotherapy and oral administration of single dose of NEPA (each containing 0.3 g netupitant and 0.5 mg palonosetron hydrochloride) 1 hour before chemotherapy.
 
 
 
 |

|                        |                                                                                                                                                                                                                                                                                                                                                                                                                                                                                                                                                                                                                                                                                                                             |

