## 5.2 Dosing Regimen

### 5.2.1 Drug Dose

- **Control Group:** 8 mg of dexamethasone is given intravenously 0.5 hours before chemotherapy, and 1 capsule of netupitant and palonosetron hydrochloride capsules (each capsule contains 0.3 g of netupitant and 0.5 mg of palonosetron hydrochloride) is taken orally 1 hour before chemotherapy.
- **Experimental Group:** 5 mg of dexamethasone is given intravenously 0.5 hours before chemotherapy, and 1 capsule of netupitant and palonosetron hydrochloride capsules (each capsule contains 0.3 g of netupitant and 0.5 mg of palonosetron hydrochloride) is taken orally 1 hour before chemotherapy.

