### 5.2.2 Drug Discontinuation Criteria During Treatment

Drug discontinuation is recommended when patients experience severe adverse events or specific types of adverse events, such as severe drug intolerance or allergic reactions.

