## **8.5 Serious Adverse Events (SAEs)**

### **8.5.1 Definition of Serious Adverse Events**

A serious adverse event (SAE) is any medical event occurring during a clinical trial that requires hospitalization, prolongs hospital stay, results in disability, affects work capacity, is life-threatening, or leads to death, or causes congenital anomalies. Adverse events meeting one or more of the following criteria are considered SAEs:

- Resulting in death;
- Life-threatening (defined as an immediate risk of death at the time of the event);
- Requiring hospitalization or prolonging hospital stay;
- Causing permanent or significant disability/functional impairment;
- Resulting in congenital anomalies or birth defects;
- Important medical events: These adverse events may not be life-threatening, but based on medical judgment, they may endanger the subject and require medical or surgical intervention to prevent any of the above outcomes.

Investigators should promptly report all SAEs, including clinical diagnosis, treatment, and outcomes, and follow up until the event is resolved, alleviated, or stabilized. Detailed records should be maintained in the original medical records and eCRF forms (including the adverse event report form; if death occurs, a death report form should be completed), and an SAE report form should be filed.

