## 11 Dropout of Subjects

All subjects who have signed the informed consent form and are screened as eligible to enter the trial have the right to withdraw from the study at any time. Subjects

who withdraw for any reason before completing the clinical trial and cannot be evaluated for safety and efficacy are considered dropouts (subjects who withdraw due to disease progression with clear medical evidence after enrollment are not considered dropouts). When a subject drops out, the investigator must record the reason for dropout in the CRF, complete all possible assessment items, and carefully document the last visit record in the CRF. For subjects who drop out due to adverse reactions and are finally determined to be related to the study drug after follow-up, this should be recorded in the CRF and notified to the investigator. Subjects who only underwent screening but did not receive a drug number and withdrew from the study are not considered dropouts. All enrolled subjects with at least one medication record will be included in the safety set and should be analyzed in the safety evaluation.

Subjects who withdraw from the study cannot re-enter the study, and their numbers cannot be reused.

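### Section 4.3 withdraws patients from the study for certain serious adverse events after a single pre-chemotherapy dose, which can end 7-day efficacy follow-up without reducing exposure

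*Protocol*

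**What the plan says.** The withdrawal list, in the synopsis and again in section 4.3, opens with "Patients will be withdrawn from the study if any of the following occurs". Its fourth item reads "Serious adverse events (SAEs) where risks outweighed benefits" in the synopsis and "Serious adverse events where risks outweighed benefits" in section 4.3. The consequence is withdrawal from the study. Stopping the drug has its own rule in section 5.2.2: "Drug discontinuation is recommended when patients experience severe adverse events or specific types of adverse events".

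Section 5.2.1 fixes the whole of the study treatment in both arms. Dexamethasone "is given intravenously 0.5 hours before chemotherapy" and one NEPA capsule "is taken orally 1 hour before chemotherapy". The primary endpoint (section 2.2.1) is no vomiting and no rescue over the 7 days after study drug. The secondary efficacy endpoints split that week into 0-24 h, 24-120 h and 120-168 h (section 2.2.2). Section 10.2 describes the trial as open-label.

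For early withdrawal, section 10.4 applies right censoring to missing dates. The principal investigator sets the censoring date case by case after reviewing laboratory tests.

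**The concern.** The withdrawal rule suits repeated dosing, where leaving the study also ends further exposure. Here, once the capsule and the injection have been given, no study drug remains to withhold. For the efficacy data, the only thing a study withdrawal can still change is how long the patient is observed.

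The trigger is a risk-benefit judgement by investigators who know the arm. Under section 8.5.1 the class of serious adverse events (SAEs) includes events "Requiring hospitalization or prolonging hospital stay", which severe emesis could do. Section 1.3.1 itself expects the lower dose to reduce side effects and perhaps to weaken control of nausea and vomiting. Missing outcomes could therefore depend on arm and on outcome. In a non-inferiority comparison of two response rates, that kind of missingness is worth avoiding when it costs little to do so.

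**Working it through.** **1. Does withdrawal reduce exposure?** The capsule is given 1 h and the injection 0.5 h before chemotherapy. Withdrawal could change study-drug exposure only in the 30 minutes between them. After the injection it cannot.

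**2. What is still collected after withdrawal?**
- Section 6.3.1: a withdrawal visit with blood tests, vital signs, examination, ECOG, adverse events and concomitant medication.
- Section 6.3.2: a safety visit 7 ± 3 days after the last dose. The window opens on day 7 - 3 = 4, so the visit can fall before 168 h.
- Section 8.4.4: adverse events to 28 days after the last dose.
- Section 8.5.1: SAEs followed until resolved, alleviated or stable.
- Section 5.3: concomitant treatments to the end of safety follow-up.

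None of these asks for a vomiting and rescue record through 168 h.

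**3. Whose outcome can be lost?**
- Vomited or took rescue before withdrawal: a known failure for overall CRR. Only CRR in the later phases is lost.
- Still in response at withdrawal: overall CRR and the remaining phases are unobserved.

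**4. What does the analysis text do with them?** Section 10.3 keeps every enrolled patient treated at least once in the modified intention-to-treat (mITT) set. The synopsis definition of mITT allows exclusions after randomization. Section 10.4 censors dates, but CRR over a fixed 7-day window is a yes/no result, and a censoring date does not give it a value.

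**5. The plan's own sample size.** Inputs from section 10.1: CRR 80% in both arms, margin 15 points, one-sided alpha 0.05, power 80%, unpooled Z.

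n per arm = (1.645 + 0.842)² × (0.8×0.2 + 0.8×0.2) / 0.15² = 6.18 × 0.32 / 0.0225 ≈ 87.9, so 88 per arm and 176 in total. With 5% attrition, 176 / 0.95 = 185.3, so 186 (93 per arm). This reproduces the stated figures.

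**6. Illustrative shift.** The protocol gives no rate of SAEs or of SAE withdrawals, so k below is an assumption. Expected responders in one arm: 0.80 × 93 = 74.4. If k patients who would have failed leave that arm's denominator, the observed CRR is 74.4 / (93 - k):

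| k | Observed CRR | Shift (points) |
|---|---|---|
| 1 | 74.4/92 = 80.9% | +0.9 |
| 2 | 74.4/91 = 81.8% | +1.8 |
| 3 | 74.4/90 = 82.7% | +2.7 |
| 5 | 74.4/88 = 84.5% | +4.5 |

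Five patients is about the whole 5% allowance for one arm (0.05 × 93 = 4.65). If instead the five would have stayed responders, CRR becomes (74.4 - 5) / 88 = 78.9%, a shift of -1.1 points.

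**7. Precision alone.** Power at one-sided 0.05 falls from 81.9% with 93 per arm to 80.0% with 88 per arm. The issue is informative loss rather than lost numbers.

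**The case against.** The strongest reply is that the rule is narrow and the protocol keeps looking at these patients. Much of that stands.

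- A reader might infer that any SAE leads to withdrawal. It does not: the risk-benefit condition must also be met, and with a single dose already given that may be seldom.
- A reader might infer that withdrawal discards all later data. The collection listed above continues, and vomiting or rescue use may be partly recovered from adverse-event and concomitant-medication records.
- A reader might infer a contradiction with section 8.5.1. None is shown. That section does not exempt withdrawn patients from SAE follow-up, and in section 4.3 only the consent item speaks of refusing further follow-up, so the two can be read together.
- A reader might infer that everyone withdrawn becomes a dropout. Section 11 limits the term to those who "withdraw for any reason before completing the clinical trial and cannot be evaluated for safety and efficacy are considered dropouts", and it asks for all possible assessments to be completed. A patient who has already vomited can be evaluated for the primary endpoint.
- Patients whose SAE is uncontrolled vomiting are already failures, so that route cannot bias overall CRR.
- The direction of any bias is not established. Less toxicity and weaker emetic control at the lower dose could pull in opposite directions.
- Scoring of a withdrawn patient is often left to the statistical analysis plan, and its absence here is not the complaint. The complaint is that the one rule the protocol does state, censoring of dates, does not suit the endpoint.

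What remains after all this is that section 4.3 does not separate stopping treatment from stopping efficacy follow-up, and no other section closes that gap.

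**Conclusion.** The point holds in limited form. After dosing, withdrawal from the study under the SAE item leaves study-drug exposure unchanged and can end efficacy observation, on an unblinded judgement. What is at risk is the overall CRR of patients still in response at withdrawal, and CRR in the later phases for anyone withdrawn.

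The 0.9 to 4.5 point shift is an upper illustration, not an estimate. It requires that 1 to 5 patients meet the rule, all in one arm, all before any vomiting or rescue, all going on to fail, and all leaving the denominator. The mITT definition in section 10.3 does not by itself remove them. The shift is zero if patients are followed to day 7, or if losses and their outcomes balance between arms. The documents therefore do not support a claim that the primary comparison will be biased by a stated amount. They do support calling this an avoidable source of informative missing data.

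**What to change.** In section 4.3 and the synopsis, separate stopping treatment from stopping follow-up. State that, unless consent is withdrawn, a patient with an SAE after dosing continues to have vomiting and rescue use recorded through 168 h and stays in the mITT analysis.

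Reconcile the repeated-dose wording with section 5.2.1. It appears in section 5.2.2, in the flowchart (dispensation on both D0 and D1), in flowchart note i (a missed dose followed by dosing the next day) and in section 6.3.2 (resuming study drug). Which clinical stopping rule applies, and how the event is managed, is for the sponsor to decide; this point takes no position on it.

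The cost is a wording amendment and, for the few patients affected, a vomiting and rescue record to day 7. These patients are already being followed for safety.
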